#### Immediate intervention effectiveness

The second set of research questions concerns the short-term effects of the intervention during the intervention phase (days 5–16). Multilevel models predicting food intake and cravings, respectively, include the factors group (intervention vs control) and (off-)training day (training day vs no training day) as predictors. In another pair of multilevel models, we use group and the number of days since the beginning of the intervention and their interaction as predictors of craving and food intake, respectively. The force applied during the training is used as a predictor for the change in craving and intake from before the start of the training.

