**Methods and analysis:**

Participants who aim to change their eating behaviour are randomised to intervention or control groups. They complete six sessions of a smartphone-based AAI, in which they push (ie, avoid) or pull (ie, approach) personalised food images. Intervention group participants always avoid foods that they personally want to eat less often and approach foods that they personally want to eat more often. In the control group, images are paired equally often with both response directions. To evaluate contextual and dynamic intervention effects, ecological momentary assessment (EMA) is measured throughout, with questions about food intake, hunger, stress, emotions, eating intentions, food craving and impulsivity twice a day. Additional EMA preintervention and postintervention measures are administered before and after the intervention phase (4 days each) with a 1-day follow-up EMA 4 weeks after the intervention. Multilevel models will examine the temporal covariance between approach bias and self-reported variables as well as short-term and long-term intervention effects on approach bias, food intake and craving.

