#### Ecological momentary assessment

Participants follow the EMA schedule for a total of 20 days. During the whole period, participants receive two prompts per day (delivered through the smartphone application m-path^69^), one just before the time a participant usually eats lunch and the other in the evening (prompted at an individualised time agreed upon with the participant to represent an end-of-day signal). Table 1 shows the questions that participants answer on those prompts and figure 3 displays the temporal sequence of the study. EMA prompts on days 1–3 of the study only contain the listed questions. On day 4 (the day before the start of the intervention) and day 17 (the day after the end of the intervention), participants receive an instruction to open the AAT application and complete a measurement AAT. On every second day during the intervention phase (days 5 through 16), participants receive an instruction to open the AAT application and complete a training AAT after completing the midday prompt. Thirty minutes after completing the midday prompt, participants receive a notification asking whether they conducted the training. On replying ‘yes’, they receive positive feedback; on replying ‘no’, they are asked to now open the AAT app to conduct the task. The number of sessions was chosen based on earlier, similar studies,^50 52^ balancing participant burden, compliance and intervention intensity.

**Table 1 T1:** Overview of EMA questions (own translations from German)

Item	Midday (all study phases)	Evening Days 1–4 and 17–20	Evening Days 5–16	Evening: follow-up
When was the last time you ate something?	X			
What type of meal was it? (breakfast, lunch, dinner, snack)	X			
How hungry are you right now?	X	X	X	
Do you feel like you have everything under control?	X			
Do you feel like you are on top of things?	X			
How optimistic do you feel right now?	X			X
How happy do you feel right now?	X			X
How lonely do you feel right now?	X			X
How depressed do you feel right now?	X			X
How angry do you feel right now?	X			X
How mad do you feel right now?	X			X
How tense do you feel right now?	X			X
How anxious do you feel right now?	X			X
How much do you want to stick to your dietary goals *for the rest of the day*?	X			
How much do you want to stick to your dietary goals *tomorrow*?		X		X
How strong has your craving for this food been *today*?*		X		X
How much of this food have you eaten *today*?*		X		X
Have you said things today without thinking?	X	X	X	X

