Have you spent more money today than you wanted to?	X	X	X	X
Have you felt impatient today?	X	X	X	X
Have you made a spontaneous decision today?	X	X	X	X
How strong has your craving for this food been *since the midday questionnaire*?*			X	
How much of this food have you eaten *since the midday questionnaire*?*			X	
How much do you expect that this task will help you reach your dietary goals?†	X†			
Throughout the whole study, how often did you push this food away from yourself?*				X
Please indicate the day your last period started.				X

All items are answered on a slider from 0 to 100 unless indicated differently in parentheses. Midday prompts remain the same across the entire study duration. Evening prompts differ depending on the study phase as indicated:.

*These items are asked alongside a food image and are repeated for each image (six ‘increase-food‘ and six ‘decrease-food’ images).

†This item is only asked after the first and the last AAT session (days 5 and 15).

AAT, Approach Avoidance Task; EMA, ecological momentary assessment.

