#### Procedure

The procedure for study participation is as follows: after interested participants contact the study team, they receive an individual participant code and a web link to the baseline questionnaire. At this point, an R-script (The function *sample* randomly outputs the number ‘1’ or ‘2’ which correspond to the conditions.) randomises participants to either the intervention or control group with the condition unknown to the study team. After a set-up call with a member of the research team within a few days of filling out the questionnaires, participants start receiving EMA prompts and AAT as described above. Figure 3 shows the timeline of the whole study. Throughout the study period, participants can contact study personnel who also monitor compliance to the EMA and AAT schedule and contact participants in case of low compliance: participants receive an email if they miss more than one of the first three AAT/AAI sessions.

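### The described training-phase models for intake and craving leave out the pre-training ratings, so their group main effect is less precise than the collected data allow

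*Protocol article*

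**What the plan says.** The section Immediate intervention effectiveness of the protocol article covers "short-term effects of the intervention during the intervention phase (days 5–16"). It describes two pairs of between-arm models, each fitted to intake and to craving:

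- First pair: "Multilevel models predicting food intake and cravings, respectively, include the factors group (intervention vs control) and (off-)training day (training day vs no training day) as" explanatory terms. No interaction is mentioned.
- Second pair: "we use group and the number of days since the beginning of the intervention and their interaction as predictors of craving and food intake, respectively".

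A third analysis in the section does refer back to the period before training: "The force applied during the training is used as a predictor for the change in craving and intake from before the start of the training". It is not described as a comparison of arms.

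Pre-training ratings exist. The abstract says: "Additional EMA preintervention and postintervention measures are administered before and after the intervention phase (4 days each"). Table 1 places the evening craving and intake items on days 1–4, and its footnote says of them: "These items are asked alongside a food image and are repeated for each image", that is, for six increase-foods and six decrease-foods. The recall period differs by phase. The item on days 1–4 reads "How much of this food have you eaten *today", while the one on days 5–16 covers only the time after the midday prompt.

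The pre/post models under Overall intervention effectiveness use the pre-training level through timepoint and its interaction with condition. Allocation is a simple draw: "The function *sample* randomly outputs the number ‘1’ or ‘2’ which correspond to the conditions". No stratification is described.

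**The concern.** Intake and craving are two of the three main outcomes, and these models are the stated test of short-term effects on them. In the first pair, the group main effect is the only between-arm term described. Without a pre-training value it compares the arms' rating levels on days 5–16 alone.

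Foods are picked for each person from recent and intended intake, so people probably differ, and stably so, in how much they eat and crave their own foods. Random intercepts describe that variation but do not remove it from a contrast between people. Simple randomisation does not balance it in any one sample. A chance difference in starting level could therefore look like an early training effect or hide one, and the standard error is wider than it needs to be.

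**Working it through.** **The plan's own figure.** The article gives about 150 participants for g=0.50 at power 0.80, and power of about 0.88 at g=0.56. Both come from resampling an unpublished data set for the group-by-time effect on approach bias. A plain two-sample normal approximation (two-sided alpha 0.05) gives 63 per arm, 126 in all, and power of 0.865 at g=0.50 with 75 per arm. That does not match, but a resampled multilevel model need not match it, so the stated figure is not shown to be wrong. The two stated powers agree with each other: Φ(2.802 × 0.56/0.50 − 1.960) = 0.881. Neither describes power for intake or craving during training.

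**Inputs here.** 75 per arm (150 split evenly, an assumption under simple randomisation); two-sided alpha 0.05; a person-level contrast in place of the food-by-day model; correlation ρ between a person's pre-training mean and training-phase mean, assumed at 0.3, 0.5 and 0.7 because the article gives none.

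**Precision of the group main effect.** Adjustment multiplies its variance by 1 − ρ². Power is Φ(d·√(75/2)/√(1−ρ²) − 1.960). An effect with 80% unadjusted power has d·√(75/2) = 1.960 + 0.842 = 2.802.

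| ρ | variance cut (ρ²) | like N = 150/(1−ρ²) | power, from 0.80 | power at 0.50 SD, from 0.865 | power at 0.30 SD, from 0.451 |
|---|---|---|---|---|---|
| 0.3 | 9% | 165 | 0.836 | 0.894 | 0.486 |
| 0.5 | 25% | 200 | 0.899 | 0.942 | 0.564 |
| 0.7 | 49% | 294 | 0.975 | 0.990 | 0.730 |

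Example at ρ = 0.5: 2.802/0.866 = 3.235; 3.235 − 1.960 = 1.275; Φ(1.275) = 0.899.

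**Chance imbalance.** The baseline difference between arms has standard error √(2/75) = 0.163 SD, so a 95% range of ±0.32 SD. The part carried into the unadjusted group effect is ρ times that: ±0.10, ±0.16 or ±0.22 SD.

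**Is such a ρ plausible?** With 4 pre-training and 12 training evenings and a day-level intraclass correlation I, ρ = I/√[(I+(1−I)/4)(I+(1−I)/12)]. Assumed I of 0.1, 0.2 and 0.3 gives ρ of 0.42, 0.61 and 0.73. With 3 pre-training evenings and I = 0.2, ρ = 0.2/√(0.467 × 0.267) = 0.57. The differing recall periods may lower these values.

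**Which terms are touched.** In a person-level simulation (75 per arm, 4 and 12 evenings, I of 0.2, 0.4 and 0.6, 4,000 runs each), the unadjusted test rejected a true null in 0.052, 0.043 and 0.047 of runs, close to the nominal 0.05. The baseline difference between arms correlated 0.60 to 0.90 with the difference in training-phase means, but only −0.03 to 0.04 with the difference in slopes over days. A stable starting level cancels from the slope, and likewise from a within-person comparison of training and off-training days.

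**The case against.** The strongest objection is that the article calls its analysis section brief and leaves the exact formulas to a preregistration that is not shown. The word used for the first pair is that the models include certain factors, which need not be exhaustive. This stands as a condition: a reader might infer that the preregistered models lack a baseline term, and the article cannot show that. Still, the pre/post models and the force analysis both name the pre-training level where they use it, and the predictor lists for these two pairs do not.

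Other objections narrow the point:

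- A reader might infer that the section ignores pre-training ratings altogether. It does not; the force analysis uses change from before training.
- A reader might infer an inflated false-positive rate. Chance imbalance is already reflected in the unadjusted standard error, and the simulation shows no inflation. The cost is lost power, and bias only conditional on the imbalance that happens to occur.
- The timing questions (group by days, training versus off-training day) are essentially untouched. The second pair's start-of-training difference is affected, but the article does not single it out as a test.
- A covariate is not the only remedy. Pre-training rows with a time term, as in the pre/post models, would also use the baseline, though here they would put whole-day and part-day ratings on one scale.
- Every ρ is assumed, and at 0.3 the gain is only about 3 to 4 points of power.

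**Conclusion.** The point holds for the group main effect of the first pair and, to some degree, for the start-of-training group difference of the second. As described, both leave out a baseline that is already collected for the same foods. For the group main effect, adjustment would cut the variance by about 9% to 49% over assumed ρ of 0.3 to 0.7. These figures rest on 75 per arm and on a person-level approximation to the multilevel model. They do not transfer exactly to the start-of-training difference, which also carries the uncertainty of the fitted slope.

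The documents do not support reading this as an invalid test, as a flaw in the group-by-days or training-day terms, or as a challenge to the sample size of 150. It is an efficiency loss on main outcomes that is cheap to avoid, and it depends on the unseen formulas not already containing the term.

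**What to change.** In both pairs of training-phase models, add as a fixed covariate the participant's food-specific mean of the same item before training, centred and with its own estimated slope: pre-training intake in the intake models, pre-training craving in the craving models. Take days 1–4, or the pre-intervention window of the pre/post models (stated there as 3 days), and name the choice. Read the group main effect from the adjusted model. Do not use a change score, because subtracting a whole-day rating from a part-day rating mixes two recall periods; an estimated slope copes with that difference. If the preregistered formulas already include such a term, one sentence in the article saying so is enough.

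The cost is one covariate per model, with no new data or participants. A simple rule is needed for foods with no usable pre-training rating, for example mean imputation of the covariate. Both should be fixed before the data are analysed by arm.

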**Figure 3 F3:**
[figure not shown]
Time schedule of the whole study period. AAI, approach-avoidance intervention; AAT, Approach Avoidance Task; EMA, ecological momentary assessment.

In addition, on day 6 and day 16 (the first day and the last day including an AAT/AAI session), participants further indicate their expectancy of how much the task will help them reach their dietary goals. Four weeks after the end of the initial 20-day EMA period, participants receive one additional EMA questionnaire and a measurement AAT in the evening. After performing this final AAT, participants indicate how often they believed they pushed or pulled each of their ‘decrease-foods’ and ‘increase-foods’.

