#### Overall intervention effectiveness

The first set of research questions relates to the effectiveness of the intervention as compared with the control condition from pretraining to post-training. To this end, we use multilevel models to predict intake of trained ‘increase’ and ‘decrease’ foods as a function of timepoint (3 days preintervention vs postintervention), condition (intervention vs control) and their interaction. Equivalent models test the intervention effect on approach biases towards—and craving for—the two food categories. To test to what degree the effect of the training intervention is specific to trained foods, we then use data from trained and untrained stimuli and add a variable that indicates whether a food appeared in the training or not (trained vs untrained) and all interaction terms to the model. This is followed up with tests to determine whether changes in the approach bias are mainly driven by changes in approach—or avoidance RTs. We further test the moderating role of intentions, baseline stimulus craving and person-level variables obtained from the questionnaires, as well as contingency awareness and expectancy by adding the relevant variable and its interaction terms to the equations. Finally, we examine the mediating effect of craving for changes in intake.

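### The training-day model names no group × training-day interaction, and its training-day factor rests on two calendars that contradict each other

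*Protocol article*

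**What the plan says.** The section on immediate intervention effectiveness states its purpose as follows: "The second set of research questions concerns the short-term effects of the intervention during the intervention phase (days 5–16"). Its first pair of models, for intake and for craving, "include the factors group (intervention vs control) and (off-)training day (training day vs no training day) as predictors". For the second pair the wording is fuller: "we use group and the number of days since the beginning of the intervention and their interaction as predictors". In the section on overall effectiveness, the pre-post model is likewise described by timepoint, "condition (intervention vs control) and their interaction".

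The section on ecological momentary assessment places training on every second day of days 5 to 16, and the abstract gives six sessions. The dates of the first and last session appear twice:

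- Table 1 footnote, on the expectancy item: "This item is only asked after the first and the last AAT session (days 5 and 15").
- Text after Figure 3, on the same item: "on day 6 and day 16 (the first day and the last day including an AAT/AAI session").

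The opening of the data analysis plan says that it is a short description and that the exact model formulas are in a preregistration, which is not at hand.

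**The concern.** Both arms do a session of the same length, with the same kinds of images, on the same scheduled days. Prompting, exposure to food pictures or being reminded of one's goals could therefore shift intake and craving on training days in both arms. What distinguishes active from sham training on those days is how much the training-day versus off-day difference differs between arms, and that is the interaction. The evening items in days 5–16 ask about the time since the midday questionnaire, and training follows the midday prompt. The data are therefore well suited to this contrast, yet the model description does not name it.

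The calendar matters because the training-day indicator is the key predictor in this model. If the document allows two codings that are mirror images, an analyst who follows the wrong passage reports the effect with its direction reversed. The calendar also decides three smaller things: whether day 5 is a training day or an off-day before any training, whether the day 17 bias test falls one or two days after the last session, and on which days expectancy, a planned moderator, is recorded.

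**Working it through.** **Session count.** Inputs: every second day, days 5–16, six sessions.

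- Table 1 footnote: 5, 7, 9, 11, 13, 15, which is six sessions.
- Text after Figure 3: 6, 8, 10, 12, 14, 16, which is six sessions.

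Both reproduce the stated six and both fit the window, so the count cannot show which was meant. The lists have no day in common, and together they cover all 12 days. Each training day on one calendar is an off-day on the other. The article also describes day 4 as the eve of the intervention and day 17 as the day after its end. The first fits a session on day 5 and the second a session on day 16. Six sessions at two-day spacing span 11 days and cannot include both.

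**What the additive model estimates.** Let G = 1 for active and T = 1 for a training day, with arms of equal size and six days of each kind. Assume, for illustration only, a baseline of 50 on the 0–100 slider and an effect of −10 confined to the active arm on training days.

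| Arm | Off-day | Training day |
|---|---|---|
| Sham | 50 | 50 |
| Active | 50 | 40 |

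Model as written, y = b0 + b1·G + b2·T:

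- b1 = average arm difference = (0 + (−10))/2 = −5
- b2 = average day difference = (0 + (−10))/2 = −5

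Now take a different truth: the active arm is lower by 5 on every day, and both arms are lower by 5 on training days. The additive model again gives b1 = −5 and b2 = −5. The two coefficients do not tell these situations apart.

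With the interaction added, b3 = (active training − active off) − (sham training − sham off):

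- first truth: (40 − 50) − (50 − 50) = −10, with b1 = 0 and b2 = 0
- second truth: (40 − 45) − (45 − 50) = 0, with b1 = −5 and b2 = −5

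**Effect of the calendar.** Take the first truth and code T from the other calendar: b3 = (50 − 40) − (50 − 50) = +10, and b1 becomes −10. The size is unchanged, the sign is reversed, and a spurious group difference appears on the days labelled off-training.

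**The case against.** The strongest reply is that the article is explicitly brief and sends the reader to the preregistration for exact formulas. To say that a model includes two factors does not exclude their interaction. That stands as a limit: the interaction may already be in the registered formula. The omission is still noticeable, because the very next sentence and the pre-post model both name theirs.

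A reader might infer that this section cannot show any immediate intervention effect. The documents do not support that. The group term is a randomised contrast averaged over days 5–16, and the same section has a group × days-since-start model. What is lost is only the part specific to training days.

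A reader might also infer that increase-foods and decrease-foods are pooled, so that opposite effects cancel. Under pooling, effects of −10 and +10 would average to 0, −10 and +5 to −2.5, and −10 and 0 to −5. But pooling is nowhere stated. The main outcomes are defined for both kinds of food. The overall effectiveness section speaks of "the two food categories" and yet lists no category predictor either, so the silence here is not evidence of pooling. It warrants a line of confirmation and no more.

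On the calendar, the app delivers one actual schedule. A sign reversal happens only if someone codes nominal days from the wrong passage, and the documents do not say that anyone will. The one- or two-day lag to the day 17 test is the same in both arms and does not bias the randomised comparison. Both points stand, but the contradiction between two current passages remains, and the preregistration's being unavailable does not explain it away.

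**Conclusion.** The calendar is wrong as written: the two passages cannot both be true, and they define training-day indicators that are exact opposites. The interaction is a free improvement. As described, the training-day model does not identify an effect of active over sham training that is specific to training days. An effect confined to the active arm on those days is split in half between the group and day terms, −5 and −5 for an assumed −10.

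This rests on equal arms, balanced days, an illustrative effect size and a literal reading of a condensed description. The sign reversal is what follows from using the wrong calendar; it is not a prediction that this will occur. The pre-post effectiveness models name their interaction, and the missing term does not affect them.

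**What to change.** 1. Reconcile the training-frequency statement, the Table 1 footnote and the text after Figure 3 with the schedule the app actually delivered. Align the days of the expectancy item with it.
2. State that training days are coded from that delivered schedule. Use dates of completed sessions only in a sensitivity analysis. As the main coding they would turn the predictor into an adherence measure observed after randomisation, because missed sessions would count as off-days and the days on which people choose to train may differ in motivation or craving.
3. Write the training-day models as group, training day and group × training-day, and name the interaction as the test of the immediate effect. Confirm that this matches the preregistered formula; if it does not, record it as a dated change.
4. Confirm in one sentence that increase-foods and decrease-foods are not pooled in these models.

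The cost is a corrected calendar and a few words of model description. No data collection, sample size or burden on participants changes.
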